### Treatment protocol

Group A received early laparoscopic cholecystectomy, within 72 hours after randomization (Figure 2).

**Figure 2 F2:**
[figure not shown]
PONCHO overview of eligibility and group allocation.

As can be seen in the time of randomization criteria, patients will be randomized 1 or 2 days prior to discharge in an attempt to prevent prolonged hospital stay due to a waiting time for cholecystectomy.

Group B received interval laparoscopic cholecystectomy, 25 to 30 days after randomization (Figure 2).

### Surgical details and quality control

Laparoscopic cholecystectomy will be performed according to the guidelines of the Dutch Society of Surgery, which include the critical view of safety technique [32-34]. Patients are operated on by, or under the direct supervision of, a laparoscopically trained surgeon with >100 laparoscopic procedures performed in the previous 5 years. There has to be supervision during the entire procedure, from incision to skin closure.

Single port cholecystectomy will not be performed in this study because there is currently limited experience with this procedure in the Netherlands. If the treating physician decides to perform a primary open cholecystectomy (laparotomy or minilaparotomy), this is allowed in the trial.

Centers may only participate if they intend to randomize at least five patients in the study and are able to perform cholecystectomy <72 hours after randomization.

Given the excellent availability of ERCP/ES in the Netherlands and the lack of experience with intraoperative cholangiography, it is not mandatory to perform an intraoperative cholangiography and, if possible, transcystic stone extraction. In centers with sufficient experience, this technique is allowed. However, laparoscopic choledochal incision and exploration is not allowed as there is insufficient experience with this technique and it is likely to be associated with more morbidity than ERCP/ES. The following data regarding intraoperative cholangiography will be collected: incidence of choledocholithiasis, percentage stones retrieved transcystically, percentage bile duct injury, additional time required, and perceived difficulty (visual analog scale 0 to 10, 5 being averagely difficult).

### Diagnosing and treating biliary pancreatitis

For imaging, in the first 24 hours of admission all patients will undergo an abdominal ultrasound aimed at detecting gallstones and/or sludge in the gallbladder and at determining the diameter of the common bile duct.

Contrast-enhanced computed tomography (CECT) is only performed if the diagnosis for acute pancreatitis is unclear. CECT performed in the first 72 hours of acute pancreatitis cannot rule out necrotizing pancreatitis. Because PONCHO is a pragmatic trial and in current clinical practice CECT is not performed routinely in these patients, CECT is not scheduled for study purposes. CECT will be performed whenever dictated by clinical circumstances based on the judgment of the treating physicians. When the patient’s condition does not improve after 1 week of hospital admission, CECT is performed to visualize the pancreas and abdomen.

ERCP/ES is performed when indicated by the treating physician.

Ursodeoxycholic acid therapy is not recommended after discharge since a recent Dutch randomized multicenter trial showed that this treatment is not effective in preventing recurrent colics and complications [35].

### Data collection and follow-up

There will be telephone follow-up contacts at 3 and 6 months after randomization. When patients are re-admitted to the hospital they are requested to contact the study coordinator. Patients are further asked to register biliary colics during the follow-up period in a gallstone diary. At 6 and 12 weeks after randomization, patients will be asked to complete the Health and Labour questionnaire [36]. Clinical data with regard to baseline characteristics and outcomes will be collected during hospital admission using a case record form. The case record form will be filled out by the local treating physicians, the study coordinator or the study nurse. The study coordinator and the study nurse are allowed to correct wrongly entered data (such as miscalculated patient age or miscalculated disease severity scores). The case record forms will be checked with source data. Only study group personnel will have access to the unblinded source data.

### Safety

An independent Data and Safety Monitoring Committee (DSMC) will evaluate the progress of the trial and will examine safety variables. Every 30 patients, individualized patient description charts including unblinded safety parameters will be presented to the DSMC. In addition to the safety endpoints, death and (serious) adverse events, the incidence of biliary leakage, Amsterdam type D [23], will be of special interest. Extra monitoring of this severe complication is clinically important. The incidence of bile duct injury (Amsterdam types A to D) has a range between 0.16 and 1.5% in the Netherlands [21].

After full explanation of the data presented by the investigators, the members of the DSMC will discuss the consequences of the data presented in the absence of the investigators. Adverse events are defined as ‘any undesirable experience occurring to a subject during a clinical trial, whether or not considered related to the intervention’ (that is, early cholecystectomy). All involved physicians will repetitively be asked to report any potential adverse events. These adverse events will be listed and discussed by the DSMC. The outcome of the meeting of the DSMC will then be discussed with the trial steering committee. The outcome will also be sent to the Institutional Review Board of the Radboud University Nijmegen Medical Centre. All possible severe adverse events will be reported to the Central Committee on Research involving Human Subjects (Centrale Commissie Mensgebonden Onderzoek) and the Institutional Review Board using the online module [37].

### Ethics

The study will be performed in accordance with the declaration of Helsinki and the Dutch Wet Medisch-wetenschappelijk Onderzoek met Mensen (Medical Research Involving Human Subjects Act). The Institutional Review Board of the Radboud University Nijmegen Medical Centre approved the protocol on 22 July 2010. Secondary approval was sought from all local ethics committees. Informed consent will be obtained from each participating patient in oral and written form prior to randomization. The PONCHO trial is registered in the ISRCTN register with identification number ISRCTN72764151.

After approval of the protocol, three amendments were approved by the ethics board. These amendments followed new regulations in the Netherlands for the reporting of (serious) adverse events and minor protocol changes. The content of the amendments are incorporated in this protocol.

### Statistical aspects

#### Sample size calculation

The PONCHO trial is a superiority trial, hypothesizing a reduction in the primary endpoint in favor of early cholecystectomy compared with the current practice of interval cholecystectomy. Data from our nationwide retrospective analysis on timing of cholecystectomy after mild biliary pancreatitis have been used to calculate the sample size [16,38]. In this previous analysis, 6.0% (*n* = 15) of 249 patients with mild biliary pancreatitis were re-admitted within 4 weeks after discharge for recurrent biliary problems prior to cholecystectomy, including 5% recurrent biliary pancreatitis. Because this study was retrospective it might have missed several recurrent complications (arbitrarily set at 20% missed endpoints: 0.2×6% = 1.2%). Furthermore, some 1% of patients may be re-admitted after cholecystectomy for recurrent biliary events. This amounts to an expected incidence of the primary endpoint in the interval laparoscopic cholecystectomy group of 8.2% (6.0 + 1.2 + 1.0). This number is quite conservative compared with the 10% re-admission rate within 4 weeks after mild biliary pancreatitis detected in our systematic review [17]. In the early laparoscopic cholecystectomy group, the re-admission rate (primary endpoint) during 6 months follow-up is set at 1% since, similar to the interval group, patients may be re-admitted for recurrent biliary events.

To demonstrate a reduction of the primary endpoint from 8.2 to 1.0% with power 80% and two-sided alpha of 5%, 132 patients will have to be included in each study group (PS Calculations, version 2.1.3; Vanderbilt University, Nashville, TN, USA). Taking a 0.5% (*n* = 2) loss to follow-up (based on the previous PROPATRIA and PANTER trials [38,39]), a total of 266 patients will have to be randomized.

#### Descriptive statistics

For dichotomous data, frequencies will be presented. Continuous data will be presented as mean and standard deviation or median and interquartile range. Baseline characteristics (all prior to randomization) are: age, sex, body mass index, etiology of pancreatitis, ASA classification, co-morbidity (that is, cardiovascular disease, pulmonary disease, chronic renal insufficiency or diabetes), predicted severity (Acute Physiology and Chronic Health Evaluation II score, Imrie score and C-reactive protein), time from onset of symptoms to randomization, and time from onset of symptoms to cholecystectomy.

#### Analyses

All analyses will be by intention-to-treat, meaning that all randomized patients are included in their initially assigned study arm, regardless of adherence to study protocol. There will be a blinded outcome assessment after the last patient in the trial has completed the follow-up. An adjudication committee blinded for treatment allocation will evaluate each patient using the raw data for the possible occurrence of the primary endpoint. Disagreements will be resolved in a plenary consensus meeting.

The primary endpoint will be compared between the treatment groups and subsequent analyses are directed at the secondary and safety endpoints. To compare the safety and efficacy of both treatment strategies, all individual endpoints of the combined primary, secondary and safety endpoints will be taken together and compared between both treatment groups.

Results are presented as risk ratios with corresponding 95% confidence intervals. Two-tailed *P* <0.05 is considered statistically significant with correction for multiple testing. In the event of imbalance between the two treatment groups a multivariable logistic regression will be used to correct for possible confounders. A *post-hoc* analysis will compare cholecystectomies with and without cholangiography.

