## Abstract

**Background:**

After an initial attack of biliary pancreatitis, cholecystectomy minimizes the risk of recurrent biliary pancreatitis and other gallstone-related complications. Guidelines advocate performing cholecystectomy within 2 to 4 weeks after discharge for mild biliary pancreatitis. During this waiting period, the patient is at risk of recurrent biliary events. In current clinical practice, surgeons usually postpone cholecystectomy for 6 weeks due to a perceived risk of a more difficult dissection in the early days following pancreatitis and for logistical reasons. We hypothesize that early laparoscopic cholecystectomy minimizes the risk of recurrent biliary pancreatitis or other complications of gallstone disease in patients with mild biliary pancreatitis without increasing the difficulty of dissection and the surgical complication rate compared with interval laparoscopic cholecystectomy.

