### Secondary endpoints

We hypothesize that early laparoscopic cholecystectomy is both effective and safe and therefore included the following secondary endpoints to assess such an effect: individual endpoints of the composite endpoint; cholangitis (Table 2); number of biliary colics registered in patient diary; difficulty of cholecystectomy (scored by visual analog scale 0 to 10; 5 being averagely difficult); conversion to open cholecystectomy (measure of technical difficulty); total length of hospital stay; need for ICU admission and total length of ICU stay; and total direct and indirect costs.

**Table 2 T2:** Secondary endpoint: definitions

**Biliary event**	**Definition**
Cholangitis	All of the following features (as previously defined) [20]:
	1) Serum total bilirubin level >40 μmol/l (>2.3 mg/dl) and/or dilated common bile duct (>6 mm) on transabdominal or endoscopic ultrasound or computed tomography;
	2) Temperature >38.5°C.
Organ failure	Failure of one or more of the following organ systems [19]:
	1) Respiratory: PaO_2_ ≤60 mmHg or need for mechanical ventilation;
	2) Cardiovascular: systolic blood pressure <90 mmHg or need for catecholamine support;
	3) Renal: creatinine level >177 μmol/l after rehydration or need for hemofiltration or hemodialysis (not including pre-existent renal failure).
Biliary leakage	Defined according to the Amsterdam criteria [23]:
	Type A: cystic duct leaks or leakage from aberrant or peripheral hepatic radicals;
	Type B: major bile duct leaks with or without concomitant biliary strictures;
	Type C: bile duct strictures without bile leakage;
	Type D: complete transection of the duct with or without excision of some portion of the bile duct.

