### Safety endpoints

The safety endpoints are: biliary leakage, Amsterdam types A to D (Table 2) [23]; need for additional surgical, radiological or endoscopic interventions [23]; other complications requiring treatment (that is, bacteremia or pneumonia); bleeding requiring reoperation or blood transfusion; and new-onset organ failure (Table 2).

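### The planned safety-and-efficacy comparison pools every endpoint: it has no risk ratio as written, and limited to binary events it offsets surgical harm with the expected benefit

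*Protocol article*

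**What the plan says.** The Analyses section of the protocol article first sets out the order of work: "The primary endpoint will be compared between the treatment groups and subsequent analyses are directed at the secondary and safety endpoints". It then adds a further comparison with its own purpose, "To compare the safety and efficacy of both treatment strategies", for which "all individual endpoints of the combined primary, secondary and safety endpoints will be taken together and compared between both treatment groups". The next paragraph gives the effect measure: "Results are presented as risk ratios with corresponding 95% confidence intervals". No rule is stated for which items enter, how they are weighted or how often a patient counts.

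The set so defined is mixed:

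- **Secondary endpoints.** The list opens with "individual endpoints of the composite endpoint; cholangitis (Table 2); number of biliary colics registered in patient diary". It also has "difficulty of cholecystectomy (scored by visual analog scale 0 to 10; 5 being averagely difficult", then conversion to open surgery, hospital stay, ICU need and stay, and costs.
- **Safety endpoints.** These are bile leakage, "need for additional surgical, radiological or endoscopic interventions", other treated complications, bleeding and new organ failure.

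The hypothesis in the abstract has two limbs: fewer biliary events, and this "without increasing the difficulty of dissection and the surgical complication rate compared with interval laparoscopic cholecystectomy".

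**The concern.** There are two difficulties.

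The first is definition. A risk ratio needs an event that each patient either has or does not have. A 0 to 10 score, days in hospital, a diary count and a cost are not events, and the article gives no cut-point that would make them so. Some items also recur. The primary components are listed again as secondary endpoints. Cholangitis is part of the primary composite and is named again among the secondary endpoints. An ERCP for a duct stone belongs to a primary component and could also be an additional endoscopic intervention under safety.

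The second is interpretation. The pool adds outcomes that early surgery is expected to reduce to outcomes that it might increase. A favourable pooled result could then coexist with a real excess of surgical harm, and could be read as support for the safety limb of the hypothesis when it says little about it.

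**Working it through.** **Inputs from the protocol article**

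- Sample size calculation: primary endpoint 8.2% interval, 1.0% early; 80% power; two-sided alpha 5%; 132 per group; 266 in total.
- Safety section: bile duct injury (Amsterdam types A to D) 0.16% to 1.5% in the Netherlands. This is the only background surgical-harm rate given.

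**Assumptions**

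- All early-arm harm rates, and interval-arm rates of 2% and 5%. The full safety list is wider than bile duct injury, so a rate above 1.5% is plausible, but the article gives none.
- Harm and biliary events are independent. The ERCP overlap shows this is only approximate.

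**Step 1. Reproduce the plan's figure.** Two proportions, pooled variance under the null, no continuity correction:

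n = [1.960·√(2·0.046·0.954) + 0.842·√(0.082·0.918 + 0.010·0.990)]² / 0.072² = 131.7, so 132 per group.

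With 0.5% loss, 264/0.995 = 265.3, so 266. Both figures reproduce, and the sample size is not in question.

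**Step 2. Literal reading.** Hospital stay, ICU stay, the diary count, the difficulty score and costs have no event definition. A risk ratio for the whole set is therefore undefined.

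**Step 3. Binary events only, each patient counted once.** Pooled risk = 1 − (1 − efficacy risk)(1 − harm risk). For 2% v 6%:

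- Interval: 1 − 0.918·0.98 = 10.0%
- Early: 1 − 0.990·0.94 = 6.9%
- Risk ratio: 0.69

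| Harm, interval | Harm, early | Harm ratio | Pooled, interval | Pooled, early | Pooled RR (early/interval) |
|---|---|---|---|---|---|
| 1.5% | 3.0% | 2.0 | 9.6% | 4.0% | 0.41 |
| 1.5% | 6.0% | 4.0 | 9.6% | 6.9% | 0.72 |
| 2.0% | 6.0% | 3.0 | 10.0% | 6.9% | 0.69 |
| 5.0% | 10.0% | 2.0 | 12.8% | 10.9% | 0.85 |

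In every row harm at least doubles and the pooled estimate still favours early surgery.

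**Step 4. Break-even.** Pooled rates are equal when early harm = 1 − 0.918·(1 − interval harm)/0.990:

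| Harm, interval | Early harm at equality | Harm ratio |
|---|---|---|
| 0.16% | 7.4% | about 46 |
| 1.5% | 8.7% | about 5.8 |
| 2.0% | 9.1% | about 4.6 |
| 5.0% | 11.9% | about 2.4 |

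**Step 5. What the separate comparisons could show.** With 132 per group (normal approximation, rough at such low counts):

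- Harm analysed alone has about 13% power for 1.5% v 3.0% and about 49% for 1.5% v 6.0%.
- The pool is also a poor efficacy test. Equal harm of 1.5% in both arms gives pooled rates of 9.6% v 2.5% and cuts power for the benefit from 80% to about 68%.

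**The case against.** The strongest reply is that the pool is an addition to the plan. The sentence just before it plans analyses of the secondary and safety endpoints. The difficulty score and conversion are named outcomes, and the safety endpoints form their own list. The monitoring committee sees unblinded safety data every 30 patients, with special attention to type D bile duct injury, and a procedure for suspected harm is laid down. A reader might infer from the arithmetic that the trial as a whole would let its efficacy benefit hide surgical harm. The document does not support that: an excess could appear in the separate results and in the committee's reviews. This part of the objection stands, and it limits the point to the pooled comparison.

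A second reply is that the reference to risk ratios implies binary events. Continuous data have their own descriptive summaries and costs their own comparison, so the sentence may mean a net comparison of events, or endpoints viewed side by side. Either is possible. Neither is what taking all endpoints together and comparing them says, and if one was intended the sentence needs rewording. An unseen analysis plan may list the events, but the rule stated here includes everything.

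A third reply concerns the repeated items. A reader might infer that double counting distorts the figures above. It does not: once each patient counts once, the overlap has no effect, and it matters only if events are summed. Listing components of a composite as secondary endpoints is ordinary practice and no fault in itself.

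The separate analyses do not fully repair the pool. They have low power for safety, so a favourable pooled result beside a non-significant safety comparison could be taken as reassurance. The stated purpose of comparing safety and efficacy is also attached to the pool.

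**Conclusion.** The point holds for the pooled comparison and no further. Taken literally it has no risk ratio; that follows from the endpoint lists and needs no assumption. Restricted to binary events, it offsets benefit against harm. With harm of 1.5% to 2% interval v 6% early, a three- to fourfold excess, the pooled risk ratio is 0.69 to 0.72 in favour of early surgery. Equality is reached only at 8.7% to 9.1% early harm.

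These figures rest on the plan's 8.2% and 1.0%, on independence, and on harm rates that are assumed except for the 1.5%, which is the top of the quoted range for bile duct injury. They show how the pool behaves and do not predict the harm of early surgery. The primary analysis and the sample size are unaffected. The change should be made, because the safety limb of the hypothesis needs a comparison that can be interpreted.

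**What to change.** Do not use the pooled comparison to judge safety. In its place, report side by side:

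1. the efficacy composite as already defined;
2. a safety composite: patients with at least one of the listed safety endpoints, each patient counted once;

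each with an effect estimate and 95% confidence interval. Show the individual safety endpoints beneath the second. Re-interventions can include ERCP for a biliary event, and the breakdown lets the reader see how much of the composite they make up without a judgement of cause for each one.

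If a net-benefit comparison is kept, define it as a supplementary binary outcome, once per patient, from a stated list of events, without the difficulty score, lengths of stay, diary counts or costs.

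The cost is revised wording and one extra table. It needs no new data and no adjudication of why an intervention was done. The safety composite will still have limited power at 132 per group, so its confidence interval should carry the interpretation and a non-significant result should not be reported as proof of safety.

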#### Additional analyses

A predefined subgroup analysis will be performed on patients with or without ES, per center and age (<75 years vs. >75 years). We will use logistic regression models to perform a formal test for interaction to assess whether treatment effects differed significantly between these subgroups.

The costs of both treatment strategies for the whole follow-up period of 6 months will be compared. All costs will be estimated based on the actual input in terms of resource use, personnel and indirect costs from loss of productivity due to sick leave (assessed by the Health and Labour Questionnaire).

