### Exclusion criteria

Exclusion criteria are: American Society of Anesthesiologists (ASA) III patients >75 years old; ASA IV and V patients; patients with ongoing alcohol abuse or chronic pancreatitis (males >3 units per day, females >2 units per day) [30]; or pregnancy.

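### The planned logistic treatment-by-center interaction test cannot inform at the planned event rates; the ES and age tests need a sparse-data method and a modest label; age exactly 75 falls in neither group

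*Protocol article*

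**What the plan says.** The protocol article, section Additional analyses, fixes three subgroup factors: "A predefined subgroup analysis will be performed on patients with or without ES, per center and age (<75 years vs. >75 years"). It also fixes the model: "We will use logistic regression models to perform a formal test for interaction". It does not name the outcome for these analyses (the primary endpoint is the natural reading), the type of test, a rule for empty cells, or any pooling of centers.

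The section Sample size calculation sets the early arm as follows: "the re-admission rate (primary endpoint) during 6 months follow-up is set at 1" per cent. For the other arm it gives an "expected incidence of the primary endpoint in the interval laparoscopic cholecystectomy group of 8.2% (6.0 + 1.2 + 1.0"). The size follows "with power 80% and two-sided alpha of 5%, 132 patients will have to be included in each study group", and after allowance for loss to follow-up "a total of 266 patients will have to be randomized". The Abstract and the section Study population give 18 hospitals, 1:1 allocation, and stratification by hospital and ES. Under Surgical details and quality control, a center may join if it intends to randomize as few as five patients.

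On age, Table 1 and the Inclusion criteria use a complete split at 75 (≤75 and >75) for the bile-duct diameter. The Exclusion criteria name only the upper side: "American Society of Anesthesiologists (ASA) III patients >75 years old".

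**The concern.** In a logistic model fitted by ordinary maximum likelihood, the treatment-by-subgroup interaction odds ratio is finite only if every arm-by-subgroup cell contains at least one event. A trial planned around one or two events in one arm rarely meets that condition with two subgroups, and in practice cannot meet it with 18. When a cell is empty, the coefficient runs off to infinity, its standard error grows faster, and a Wald P value drifts towards 1 whatever the data show.

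The ES analysis is not incidental. The section Randomization gives the possibility of this subgroup analysis as a benefit of stratifying on ES. A result that comes from the fitting method rather than from the patients would be of no use there.

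Separately, groups labelled below 75 and above 75 do not cover everyone who was randomized.

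**Working it through.** **Inputs.** From the protocol article: rates of 1.0% and 8.2%, 80% power, two-sided 5%, 266 randomized (133 per arm), 18 hospitals. Assumed, because the document does not give them: the shares of patients in the ES and age subgroups (shown as ranges), and centers of equal size.

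**1. The plan's own sample size.** With mean rate 0.046 and pooled variance under the null:

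n = [1.960·√(2·0.046·0.954) + 0.842·√(0.082·0.918 + 0.010·0.990)]² / 0.072² = (0.5807 + 0.2456)² / 0.005184 = 131.7, so 132 per arm. This agrees with the protocol.

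**2. Expected events.** Early: 133 × 0.010 = 1.33. Interval: 133 × 0.082 = 10.9. Total: about 12.2.

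**3. Center.** Patients per center and arm: 133/18 = 7.39.
- Expected events per center: 7.39 × 0.010 = 0.074 early, 7.39 × 0.082 = 0.61 interval.
- P(at least one early event in a center) = 1 − 0.99^7.39 = 0.072. Interval: 1 − 0.918^7.39 = 0.469.
- Centers with no early event: 18 × 0.928 = 16.7. Centers with no event at all: 18 × 0.928 × 0.531 = 8.9.
- P(every center has an event in both arms) = (0.0716 × 0.4686)^18, about 3 × 10⁻²⁷. At least 18 early events would be needed, against 1.33 expected.
- Likelihood-ratio test on 17 degrees of freedom (critical value 27.6), simulated at the planning rates with 7 or 8 patients per center and arm, 4,000 runs: 0% rejections with no interaction. When the benefit was absent in 3, 6 or 9 of the 18 centers, rejections stayed below 1%.
- At assumed rates of 5% and 18%, about 18 × 0.95^7.39 = 12 centers still have no early event, and the all-cells probability is about 10⁻¹¹. The conclusion for center therefore does not hinge on the planning rates.

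**4. ES and age: is the odds ratio finite?** P(0 early events) = 0.99^133 = 0.263 and P(exactly 1) = 133 × 0.01 × 0.99^132 = 0.353. In either case at least one early-arm cell is empty, so in at least 62% of trials no two-group interaction odds ratio is finite, whatever the split. For a subgroup of a patients per arm, the chance that all four cells are filled is

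(1 − 0.99^a)(1 − 0.99^(133−a))(1 − 0.918^a)(1 − 0.918^(133−a)).

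| Assumed share | a | All four cells filled |
|---|---|---|
| 8% | 11 | 4.5% |
| 10% | 13 | 5.8% |
| 20% | 27 | 14% |
| 30% | 40 | 19% |
| 50% | 66 | 24% |

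These figures take the same treatment effect in both subgroups. They also depend on the rates. At 2% versus 10% the probability is 16% (share 10%) or 55% (share 50%). At 5% versus 18% it is 45% or 94%.

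**5. ES and age: does a likelihood-ratio test work?** Simulated at the planning rates, it rejects in about 3–4% of trials when there is no interaction. With the benefit wholly absent in the subgroup (8.2% in both arms there), one set of runs gave 30%, 39%, 44% and 46% for shares of 10%, 20%, 30% and 50%. Repeat runs differ by a point or two, hence about 28–45%. Under that alternative all four cells are filled in about 30–57% of trials.

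**6. Age.** Below 75 and above 75 together exclude 75. The split in Table 1 and the Inclusion criteria does not.

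**The case against.** The strongest counter-argument is that an infinite coefficient is not a failed test. A reader might infer from the table above that the ES and age tests cannot be computed in most trials. The document does not support that. It asks for a formal logistic interaction test and names neither a Wald test nor a finite odds ratio. The likelihood-ratio test is a standard form, stays defined with an empty cell, and holds its type I error. The cell-filling figures also assume no interaction, the planning rates and unknown subgroup shares. The protocol itself calls its interval rate conservative against the 10% in its systematic review. This objection stands: for ES and age the defect is an unstable estimate and low power, not an impossible test.

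It can also be said that the choice of test and rules for sparse cells belong in an analysis plan that is not shown. For ES and age that is largely fair. For center it is not, because the article itself commits to a formal interaction test on that factor, and no choice of test makes 1.3 expected early events informative about 18 centers.

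Two further inferences go too far. Nothing says that patients aged 75 will be dropped; the section Analyses promises that everyone randomized is included, so the age labels are a slip that conflicts with it. And nothing shows that a non-significant interaction would be presented as proof of a consistent effect.

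**Conclusion.** The point holds for center without qualification. At the planned rates the test cannot give finite estimates and has essentially no chance of rejecting, and higher assumed rates of 5% and 18% do not make every center estimable.

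For ES and age it holds in a limited form. All four cells are filled in about 4–24% of trials for shares of 8–50%, so Wald results would be unreliable. A likelihood-ratio test remains valid, with power of about 28–45% even against complete loss of benefit in a subgroup of 10–50%. This part rests on the planning rates, the assumed shares and the primary endpoint being the outcome.

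The gap at age 75 is real, touches few patients and is editorial. These are additional analyses: the primary comparison stands, and the sample size of 132 per arm reproduces.

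**What to change.** - **Center:** replace the interaction test by a table of events and patients by center and arm.
- **ES and age:** name a likelihood-ratio or Firth-penalized logistic interaction test and exclude Wald tests. Stay on a relative scale, in line with the risk ratios and logistic models already planned. A test of equal risk differences would ask another question, because baseline risk may differ by ES (the section Randomization describes ES as protective). Show events per subgroup and arm with confidence intervals, and label the result exploratory and low-powered.
- **Age:** define the groups as ≤75 and >75, as in Table 1 and the Inclusion criteria.

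The cost is a few lines of wording in the protocol or analysis plan. No patients, visits or data items are added, and the only analysis lost is a center test that could not have informed.
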